### Randomization

Baseline data of participants will be collected within 2 weeks and evaluated before random assignment. Participants will be assigned to the TA group, the MC group, or the SA group at a ratio of 1:1:1. To ensure the equality of random distribution, the generation of random sequences will be performed by the Acupuncture Research Institute, who will not participate in this study. Random numbers and grouping results will be saved in opaque envelopes by the staff who performed the randomization. All envelopes will be kept by staff who will not participate in the study. The research assistant will open the envelopes to assign them in the order in which they are registered.

### Blinding

Because of the characteristics of acupuncture, the acupuncturists in this study cannot be blinded to the assignment, but the participants can be blinded. The treatment, testing, and follow-up of each group will be implemented independently, with no intersection between each group. The sham acupuncture in this study can guarantee a painful effect, similar to acupuncture, but does not penetrate the skin; sham acupuncture will allow for the better blinding of the participants. In addition, participants in the TA and SA groups will be asked three questions at the end of the 12 weeks to test the blinding effect: ‘Do you have confidence in this treatment?’ ‘Would you recommend this therapy to your friends?’ ‘Can you accept this kind of acupuncture?’ The participants will choose ‘Yes’ or ‘No’ to answer the questions. The data will be analysed at the end of the study. If the results are not significant, then it can be concluded that the blinding was sufficient. To ensure the uniformity of ultrasound examination and blood testing, all ultrasound examinations will be completed by a doctor with over 10 years of vascular ultrasound work experience. The Department of Clinical Laboratory of Guangdong Provincial Hospital of Traditional Chinese Medicine is responsible for the whole blood testing process. Both the ultrasound doctor and clinical laboratory will be blinded to the assignment. Collectors and statisticians responsible for collecting data and statistics will be blinded to the assignment.

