### Sample size

This is a three-arm study. In our search for previous studies of the effects of acupuncture on the carotid atherosclerotic plaque, it was found that most of the studies were two-arm studies of acupuncture versus drugs. There is a lack of high-quality clinical research. In addition, the effect of acupuncture exhibits a significant correlation between acupoints. Therefore, it is not appropriate to use the previous acupuncture clinical research literature data to estimate the sample size. Furthermore, this is a pilot study to guide future randomized controlled trials and to test the feasibility of the protocol. Considering that there are many clinical blood tests in the study, we will choose the clinical minimum sample size of 30 individuals for each group to reduce the burden of detection of the subjects. The maximum dropout rate within the intervention is expected to be approximately 15%. The total number of patients needed to be randomized is therefore 105 (35 for each group).

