### Statistical analysis

This study will use per-protocol (PP) and intention-to-treat (ITT) analysis principles. ITT will include all subjects who participated in at least one treatment, including participants who dropped out. Missing data for participants who dropped out will be supplemented with the most recent data. The PP principle will analyse all participants’ data that conform to the study protocol, and those of individuals who did not conform to the protocol will not be included.

The data will be analysed by professional statisticians with SPSS 20.0 software (IBM SPSS Statistics, IBM Corp, Somers, NY, USA). First, we will describe the baseline data, such as age, blood pressure, course of the disease, BMI, and sex, and compare the baseline data between the three groups. The continuous variables will be presented as the mean ± standard deviation (SD), and the categorical variables will be presented as the composition ratio and rate.

Continuous variables that conform to a normal distribution will be analysed by ANOVA, and the non-conforming data will be analysed using the rank sum test. Categorical variables will be analysed using the chi-square (*χ*^2^) test or Fisher’s exact test. The confidence interval (CI) will be estimated at 95%, and the significance level will be set at 0.05. A *P* value < 0.05 will be considered statistically significant. The adverse data will be recorded and analysed for the relationship with acupuncture. We will calculate the dropout rate and analyse the reasons for dropping out.

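### The week-12 blinding check measures treatment credibility rather than perceived allocation, and a non-significant result on it cannot show that participant blinding was sufficient

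*Protocol article*

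**What the plan says.** The Blinding section of the protocol article says that acupuncturists cannot be blinded but participants can, and describes the check: "participants in the TA and SA groups will be asked three questions at the end of the 12 weeks to test the blinding effect". The questions, each answered Yes or No, are "Do you have confidence in this treatment", "Would you recommend this therapy to your friends" and "Can you accept this kind of acupuncture". The decision rule follows: "If the results are not significant, then it can be concluded that the blinding was sufficient".

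Under Statistical analysis, "Categorical variables will be analysed using the chi-square" test or Fisher's exact test, and "the significance level will be set at 0.05". Under Sample size, "we will choose the clinical minimum sample size of 30 individuals for each group", raised to 35 randomized per arm for an expected dropout of about 15%. That number is a chosen minimum, not the result of a power calculation.

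The article gives no margin, estimate or confidence interval for the blinding conclusion, and no rule for combining the three answers. Nothing elsewhere in it adds a guess question or qualifies the rule.

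**The concern.** The rule has two separate faults.

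**What is measured.** The three items capture credibility and acceptability. A participant who has worked out that the needle was sham can still answer Yes to all three. A TA participant who feels better may answer Yes more readily with blinding fully intact. The answers therefore do not identify blinding in either direction, and a larger sample would not cure this.

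**How the result is read.** Failure to find a difference is treated as a demonstration that there is none. In a small sample that mostly reflects low power, and fewer completed questionnaires make the criterion easier to pass.

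At stake is the claim of participant blinding in TA versus SA, the placebo comparison the Study design section sets up to judge acupuncture's efficacy. The Sample size section also says this pilot is to guide later trials and test feasibility, so an unsupported statement that the sham blinded participants could carry forward into the next design.

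**Working it through.** **Inputs from the protocol.** Alpha 0.05 (two-sided assumed, as sidedness is not stated); chi-square or Fisher's exact test; 30 per arm after dropout, 35 randomized.

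**Input not in the protocol.** The true Yes rates. The values below are assumptions chosen to show a range.

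**1. The plan's own figure.** 30 × (1 + 0.15) = 34.5, rounded up to 35 per arm and 3 × 35 = 105 in total, which matches. Dividing instead gives 30 / 0.85 = 35.3, or 36 per arm. The difference is immaterial here, and 30 to 35 is a fair range for the number answering in each arm.

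**2. Power of one question.** With X ~ Bin(n, p₁) in TA and Y ~ Bin(n, p₂) in SA, power is the sum of P(X = i)·P(Y = j) over all tables (i, j) with P < 0.05. Exact enumeration, with the chi-square test uncorrected, gives:

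| Assumed Yes rates | n per arm | Fisher | Chi-square | Missed (1 − power) |
|---|---|---|---|---|
| 90% vs 80% | 30 | 0.096 | 0.194 | 0.806–0.904 |
| 90% vs 80% | 35 | 0.129 | 0.219 | 0.781–0.871 |
| 80% vs 60% | 30 | 0.298 | 0.392 | 0.608–0.702 |
| 80% vs 60% | 35 | 0.357 | 0.453 | 0.547–0.643 |
| 90% vs 70% | 30 | 0.372 | 0.499 | 0.501–0.628 |
| 90% vs 70% | 35 | 0.455 | 0.565 | 0.435–0.545 |
| 70% vs 30% | 30 | 0.838 | 0.896 | 0.104–0.162 |
| 70% vs 30% | 35 | 0.882 | 0.924 | 0.076–0.118 |

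Over the two 20-point scenarios the miss rate runs from about 43% to 70%. For 80% power the normal approximation needs 82 per arm (80% vs 60%), 62 (90% vs 70%) or 199 (90% vs 80%).

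**3. What can pass.** Observed counts of 27/30 vs 20/30 (23 points apart) give Fisher P = 0.057, and 24/30 vs 16/30 (27 points) give P = 0.054. Both would count as sufficient blinding by Fisher's test. The uncorrected chi-square gives z = 0.2333 / √(0.7833 × 0.2167 × 2/30) = 2.19 and z = 0.2667 / √(0.6667 × 0.3333 × 2/30) = 2.19, so P = 0.028 in each case. The same data would pass or fail according to which of the two named tests is used.

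**4. Three questions.** Suppose all three must be non-significant, each has the 80% vs 60% gap at n = 30, and answers are independent. The pass probability is then 0.608³ = 0.22 (chi-square) to 0.702³ = 0.35 (Fisher). Positively correlated answers would put it between these and the single-question 0.61 to 0.70. In the other direction, if any one significant result counts as failure and there is no true difference, three independent tests at a nominal 0.05 give 1 − 0.95³ = 0.14 false alarms.

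**5. Precision of a guess question.** For a per-arm index 2p − 1 with no don't-know answers and p = 0.5, the 95% half-width is 1.96 × √(1/n): 0.36 at n = 30 and 0.33 at n = 35. Even the right question would describe blinding here, not establish it within a narrow margin.

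**The case against.** The strongest reply concerns consequence. Plaque volume and grey-scale median are ultrasound measures, and the named secondary outcomes are ultrasound or laboratory measures; none is patient-reported. The Blinding section also blinds the ultrasound doctor, the laboratory, the data collectors and the statisticians. The check enters no efficacy analysis, so correcting it changes no efficacy estimate, P value or sample size. This stands and bounds the point. What remains is indirect: a participant who detects sham could change diet, which the Limitations section says cannot be ignored for lipids, or could withdraw. The documents do not allow that route to be sized.

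A second reply concerns the figures. A reader might take the 43% to 70% as the chance that the trial certifies blinding that has failed. The documents do not support that reading. Since the items do not measure blinding, a 20-point gap in Yes answers may reflect perceived benefit with blinding intact. The Yes rates are assumptions, and the figures are for one question while the protocol asks three without saying how they combine.

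Nor is it right that the rule would always pass failed blinding: a 40-point gap in answers would be caught in 84% to 92% of trials.

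None of this rescues the inference from non-significance, which is written into the protocol as a rule and is not a detail left to an analysis plan.

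**Conclusion.** The concern holds in a bounded form. The check cannot support its stated conclusion, because the items address a different construct and because a non-significant difference is read as proof. The rule could, and often would, declare blinding sufficient without evidence for it.

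The size rests on two-sided alpha 0.05, 30 to 35 answers per arm and the assumed Yes rates in the table. The first fault, the wrong construct, depends on none of these.

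A reader might infer that the TA versus SA efficacy result is itself undermined. The documents do not support that, given outcomes read by blinded assessors. The flaw limits what the trial may say about participant blinding. It is wrong as written and cheap to correct, but it does not threaten the main analysis.

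**What to change.** 1. Delete the sentence that infers sufficient blinding from non-significance. This can be done at any stage of recruitment.
2. Relabel the three questions as credibility and acceptability items, and report Yes proportions by arm and the TA–SA difference with 95% confidence intervals.
3. For TA and SA participants still to be assessed, add one question on perceived allocation (real, sham, don't know). Report the guesses by arm with a blinding index, such as Bang's, and its 95% confidence interval, as a descriptive estimate with no pass mark. The half-width of about ±0.36 at n = 30 assumes no don't-know answers.

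**Cost.** One question on an existing form and a revised analysis sentence; success of blinding can no longer be claimed from a P value. The Trial status section reports recruitment from July 2018 and 42 participants by October 2019, so some may already be past week 12 and guess data may be incomplete. The change must be reported to the ethics committee and the registry, as the Ethics and dissemination section requires. A week-12 guess can itself be coloured by perceived benefit, and raising the possibility of sham before the week-24 assessment may prompt suspicion during follow-up. Both should be acknowledged when the guesses are reported.

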## Intervention

The protocol design was based on previous clinical research and the classic theory of Chinese medicine. All operations adhered to the Standards for Reporting Interventions in Clinical Trials of Acupuncture (STRICTA) standard [21]. Acupoints applied in the RA and SA groups are the same as those listed in Table 1 and Fig. 3, according to the WHO Standard Acupuncture Locations guideline [22]. All acupuncturists who will take part in the research will be qualified to perform acupuncture with at least 5 years of study experience or 3 years of related work experience. Before implementation, all the researchers engaged in this study will participate in a unified training programme together. The groups will undergo the treatments separately twice per week for 24 treatments in total. In order to ensure the rights and interests of the patients and meet the ethical requirements, the subjects are allowed to use the treatment for diseases (such as cervical spondylosis, pain, insomnia, and fever) which are not closely related to atherosclerosis during the study period. It should be noted that the treatment received by the patients cannot interact with the drugs taken in the study, and the patients cannot receive any other acupuncture treatments so as not to interfere with the evaluation of the efficacy of the interventions included in the study.

**Table 1 Tab1:** Acupoints in both the TA group and the SA group

Name	Locations
*NEIGUAN* (PC6)	On the palmar side of the forearm, 2 in. superior to the transverse crease of the wrist, between the palmaris longus tendon and the radial wrist flexor tendon.
*RENYING* (ST9)	Lateral to the laryngeal prominence of the cervical region, the anterior margin of the sternocleidomastoid, at the fluctuation place of the common carotid artery.
*BAIHUI* (DU20)	On the median line of the head, 5 in. superior to the anterior hairline, at about the middle of the connecting line between both auricular tips.
*YINTANG* (EX-HN3)	At the middle between the two eyebrows on the forehead.
*YANGLINGQUAN* (GB34)	On the lateral side of the shank, in the depression anterior and inferior to the head of the fibula.

**Fig. 3 Fig3:**
[figure not shown]
Acupoint diagram of the protocol. The eight acupoints used in the protocol visually are shown. NEIGUAN (PC6), RENYING (ST9) (both sides), BAIHUI (DU20), YINTANG (EX-HN3), and YANGLINGQUAN (GB34) (both sides) are applied in total. The specific location of these acupoints is listed in Table 1

### TA group

Before undergoing acupuncture, patients will be asked to lie in the supine position in a quiet environment. First and foremost, the acupuncturist will sterilize his or her fingers and the skin near the acupoints with 0.5% iodine. Then, quick needle insertion will be performed with a stainless steel needle (30 × 25 mm, Huatuo, Suzhou, China) by skilled acupuncturists. The depth of insertion is flexible and depends on the location of the acupoints and the figure of the patient. NEIGUAN (PC6), YANGLINGQUAN (GB34), and RENYING (ST9) will be inserted first, while BAIHUI (DU20) and YINTANG (EX-HN3) will be inserted subsequently. After that, the needle will be twirled gently and retained for 30 min after the arrival of Qi. When withdrawing the needles, acupuncturists will be asked to press the pinholes with cotton swabs for 2 min in case of bleeding, especially for the RENYING (ST9) acupoint.

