### Primary outcome

Vessel plaque quantification (VPQ) is preferred for observing plaque morphological characteristics as a non-invasive assessment method [23]. The vessel plaque quantification technique has a substantial advantage over traditional two-dimensional ultrasound, which has been used for vascular event risk prediction. There are two aspects to be measured by the same sonologist: the total PV of the carotid artery on each side and the grey-scale median (GSM), which can indicate the average hardness of plaques proportionally [24, 25]. Both the PV and GSM will be assessed on weeks 0, 12, and 24 on each side.

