### Data collection and management

This study will collect population data from eligible participants before the first treatment; these data include name, age, duration, occupation, blood pressure, sex, and body mass index (BMI). Drug and acupuncture adverse reactions will be recorded during the treatment and follow-up periods based on the reaction of the participants. At weeks 0, 12, and 24, data on carotid ultrasound, blood lipids, platelet aggregation, fibrinogen, platelet count, and apolipoprotein A-IV will be collected. The data collection will be performed by three staff members who will not take part in acupuncture treatment, index evaluation, statistical analysis, or grouping. The data collection and entry will be performed independently by two of the staff members and finalized by a third staff member. The main investigators, acupuncturist, sonographers, and laboratory staff will not be involved in data collection.

All data must be saved in paper with identification codes in seal, while electronic data is saved on the ResMan Research Manager of the Clinical Trial Management Public Platform, and photo formats are also named with identification codes to ensure authenticity and integrity. All data must be saved in paper, electronic, and photo formats to ensure authenticity and integrity. The data should be kept for at least 5 years after the article is published. A data monitoring committee was also set up in this study, composed of experts with good clinical research experience in the Department of Acupuncture of Guangdong Provincial Hospital of Traditional Chinese Medicine. Experts will regularly monitor research progress, data, participant management, distribution, and more. The committee is independent from the fund sponsor and has no conflicts of interest. Researchers who take charge in the data collection and entry will have access to the interim results and report to main investigators if necessary. Consequently, the main investigators will make the final decision to terminate the trial after discussion.

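### The stated blinding of the sonologist is at risk at the week-12 scan, because only the TA arm has its skin pierced at a point over the carotid artery being scanned

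*Protocol article*

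**What the plan says.** All references are to the protocol article.

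- **Blinding:** "Both the ultrasound doctor and clinical laboratory will be blinded to the assignment". The sham needle is described there as "similar to acupuncture, but does not penetrate the skin". The only blinding check is a set of three questions put to TA and SA participants at the end of the 12 weeks.
- **Primary outcome:** "There are two aspects to be measured by the same sonologist: the total PV of the carotid artery on each side and the grey-scale median". Timing: "Both the PV and GSM will be assessed on weeks 0, 12, and 24 on each side".
- **Intervention, Table 1:** ST9 is located at "the anterior margin of the sternocleidomastoid, at the fluctuation place of the common carotid artery". The legend to Fig. 3 says it is used on both sides.
- **TA group:** on withdrawing the needles, acupuncturists are to "press the pinholes with cotton swabs for 2 min in case of bleeding, especially for the RENYING (ST9) acupoint".
- **Safety assessment:** bleeding and redness are among the reactions that acupuncture may cause.
- **SA group:** a tube is fixed with double-sided adhesive at the same acupoints, and a blunt needle is used.
- **MC group:** tablets; no needling is described.
- **The basis of treatment sequence selection:** two sessions a week for 12 weeks, 24 in total.
- **Data collection and management:** "photo formats are also named with identification codes to ensure authenticity and integrity".

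**The concern.** The acupuncturists know the allocation, and MC participants know that they take tablets. Blinded ultrasound measurement is therefore the main protection for PV and GSM. The intervention may leave a sign of allocation, in one arm only, at the place where the blinded person works. A sonologist who sees puncture marks on the neck can infer TA, and one person produces both primary outcomes on both sides. If that knowledge moved the readings, even unintentionally, the bias would enter both primary outcomes at the end-of-treatment assessment. The article describes a blinding check for participants but none for the sonologist.

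**Working it through.** **1. Do the described features meet at the same place and time?** No figure in the article bears on this, so the sections are set side by side.

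| Question | What the article gives | Section |
|---|---|---|
| Who measures PV and GSM? | One sonologist, declared blinded | Blinding; Primary outcome |
| Where is ST9? | On the neck over the common carotid, both sides | Table 1; Fig. 3 legend |
| Where is the scan? | Carotid artery, each side | Primary outcome |
| Is the skin pierced at ST9? | TA yes; SA no; MC no needling described | TA group; Blinding; MC group |
| Are local signs possible? | Bleeding, redness | TA group; Safety assessment |
| When are the sessions? | 2 × 12 = 24 over 12 weeks | Treatment sequence |
| When are the scans? | Weeks 0, 12 and 24 | Primary outcome |

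If a course runs to schedule, its last sessions fall in week 12, when the scan is due. Evenly spaced sessions would be about 7/2 = 3.5 days apart. The article gives no interval between the last session and the scan.

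**2. Which comparisons are exposed, and how?**

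- TA versus SA: through skin marks only. These participants are themselves blinded, so they cannot tell the sonologist which of the two they received.
- TA or SA versus MC: through skin marks, and also through remarks, because MC participants know that they take tablets.

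**3. Which scans are exposed?** Week 0 precedes treatment. Week 24 is 12 weeks after treatment ends and is largely unaffected by skin marks. The exposure is at week 12.

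**4. Illustration of size.** The inputs from the article are 35 per arm randomised, a planning minimum of 30 per arm (Sample size) and a significance level of 0.05 (Statistical analysis). As a check on the planned numbers, 30 × 1.15 = 34.5, rounded up to 35, and 3 × 35 = 105, as stated. My assumptions are a two-sided test of two means by normal approximation, no true effect, and an average reading shift *b* (in SD units) over all TA participants.

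- SE = √(2/n): √(2/35) = 0.239 and √(2/30) = 0.258.
- Rejection rate = Φ(b/SE − 1.96) + Φ(−b/SE − 1.96).
- Example with n = 35, b = 0.2: b/SE = 0.837, so Φ(−1.123) + Φ(−2.797) = 0.131 + 0.003 = 0.133.

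| Average shift in TA | 35 per arm | 30 per arm |
|---|---|---|
| 0 | 5.0% | 5.0% |
| 0.1 SD | 7.0% | 6.7% |
| 0.2 SD | 13.3% | 12.1% |
| 0.3 SD | 24.1% | 21.3% |

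The shift is an average over the arm. If only half of the TA participants had visible marks and their readings moved by 0.2 SD, the average would be 0.5 × 0.2 = 0.1 SD and the rate about 7%.

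**The case against.** The strongest reply is that nothing in the article contradicts the blinding statement outright. Scan windows and reading procedures are details that a condensed article may leave to a full protocol. Much of this stands, and it limits the point as follows.

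- **Fresh punctures.** A reader might infer that TA participants arrive with punctures a few days old at most. The article does not say so. It gives no session-to-scan interval and no duration of marks. Participants also count as compliant with 80% of sessions (0.8 × 24 = 19.2, so 20), so a last session in week 12 is not assured for everyone.
- **Expected bleeding.** The pressure on the pinholes is a precaution against bleeding, and the listed reactions are possibilities. Bruising is not mentioned.
- **TA as the only marked arm.** SA adhesive may leave its own marks. That need not restore blinding, since such a mark may look different from a puncture and MC has neither.
- **The illustration.** The shifts are assumed, and the calculation is a pairwise normal approximation, whereas the plan names ANOVA or a rank sum test. It shows sensitivity to bias and does not estimate bias.
- **Stored images.** A reader might take the coded photo formats to mean that re-measurable 3D datasets are already kept. The article does not say that.

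What survives is more than a missing detail. The article makes a positive statement of blinding and describes an intervention that works against it, and none of the measures it describes keeps the sonologist from seeing the neck. The separate handling of each group, stated under Blinding, does not do so either.

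**Conclusion.** The point holds as a risk. The sonologist's stated blinding can be compromised at week 12 by the site and schedule of TA needling, for both primary outcomes. It would be wrong to conclude that blinding has failed or will fail. That would need the interval from last session to scan, the persistence of marks and evidence that the sonologist's readings respond to them, and the article gives none of these. The size of any bias is unknown. The error rates of about 7%, 13% and 24% (7%, 12% and 21% with 30 per arm) rest entirely on assumed average shifts of 0.1, 0.2 and 0.3 SD. The sample size is not affected. This is a worthwhile, inexpensive improvement, and it suits a pilot meant to test the feasibility of the protocol before larger trials.

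**What to change.** In the Blinding and Primary outcome sections, state that:

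1. the vessel plaque quantification datasets are stored under the identification code, and the same sonologist measures PV and GSM later, in batches, with arm and visit masked;
2. this applies to all participants whose datasets were kept, and the report says which participants were measured this way;
3. the week-12 scan has one window counted from the end of the 12-week treatment period, identical in all three arms (a window counted from the last session would have no meaning for MC);
4. the sonologist's guess of arm is recorded at week 12.

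**Cost:** storage, delayed reading sessions and a defined visit window; no extra reader and no change to treatment. The sponsor must first confirm that re-measurable datasets are kept.

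**Downsides:** recruitment began in July 2018 and 42 people had taken part by October 2019, so measurement methods may be mixed if the earlier datasets were not kept. Image acquisition stays unmasked, because the sonologist still sees the neck during the scan.
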